### Blinding

The research assistants responsible for assessing primary and secondary outcomes will remain blinded to the patients’ group assignment throughout the study. The physician responsible for making clinical management decisions for those in the SMASK intervention arm will remain blinded to which patients are enrolled in the trial as enhanced attention SC subjects, as they are merely providing SC. However, the participants will not be blinded to their group assignment, as we provide a BP monitor and smartphone as needed to those in the intervention group.

### Data Collection and Management

Instruments for data collection are listed in Table 1. Data captured electronically will be transmitted using secure encrypted algorithms and housed on site in a secure HIPAA-compliant relational database.

### Statistical Analyses

#### Primary Outcome Measures

The ITT analysis set will be determined in accordance with the International Conference on Harmonization E9 Guideline “Statistical Principles for Clinical Trials” [70] and will include all randomized subjects. For all subjects included in the ITT analysis set, all available data points will be included in the model. We chose a mixed-effects model approach because this method is a standard method in RCTs and can handle missing data and account for correlated data such as repeated measurements within patients or patients clustered within providers [71-73].

We propose a two-level analysis strategy: Our primary analysis will include the simple mixed-effects model containing the fixed time and intervention group, time, and time-by-intervention as primary independent variables (fixed effects) and MD as a random effect to account for clustering. The main analysis will compare the two intervention groups (SMASK vs SC) at the primary time point outcome at 3 months. We will estimate medication adherence score changes and changes in resting and 24-hour BP for each subject over the trial (preintervention and 1, 3, 6, and 12 months) and the within-subject longitudinal trajectories (eg, slopes) and summarize the mean longitudinal trajectory within each group. Intraclass correlations and variance estimates will be obtained for the efficacy outcomes and covariance structure of the longitudinal scores to determine the sample size (and hence adequate power) for a future effectiveness RCT.

In secondary/exploratory analysis for aim 1 outcomes, the potential influence of *a priori* specified covariates on these models will be explored, including self-determination theory tenants, demographic and clinical characteristics, and comorbidities. In an additional exploratory analysis, effect modifications of covariates will be examined through inclusion of covariate-by-group interaction terms in the multivariable models.

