### Calculation of Adherence Score

A detailed description of the medication adherence score calculation by Russell et al is available elsewhere [50]. We will employ a modification of the algorithm to allow for dosing schedules other than the twice daily schedule. Our subjects will be instructed that to be considered fully adherent, their medications have to be taken within a 3-hour window of the prescribed dosing time. A dose taken within the 3-hour window will be assigned a full score for that dosing time, a dose taken outside the 3-hour window but within a 6-hour window will be assigned a half score for that dosing time, and a missed dose will be assigned a score of 0. Each subject will be assigned a score from 0.0 to 1.0 for each day. The scores for each subject will be averaged over each week.

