### Proposed Sample Size

To evaluate SMASK treatment efficacy, 80 patients will be recruited and randomly assigned to either SMASK or SC. The primary outcomes of aim 1 include the proportion of patients with >0.90 medication adherence scores (based on the date/time stamped scores from the electronic trays) and proportion of patients meeting and sustaining adherence the KDIGO guidelines for clinic-based SBP control (<130 mm Hg). In intent-to-treat (ITT) analysis, with 40 patients per group, a two-sided Chi-square test (α=0.05) will have >90% power to detect a difference of 35% in proportions of those who are medication adherent (or meeting and sustaining adherence to the KDIGO BP guidelines) in the SMASK group compared to those in the SC group at the 3-month time point. A difference of 35% in medication adherence between the groups would be considered clinically relevant and warrant changes in clinical practice. Conservative estimates for medication adherence and expected BP control proportions will be used for power calculations. This approach was taken with a small pilot study, and CIs on effect sizes were quite large. Medication adherence observed in the SMASK 3-month feasibility study was 89% (versus 0% in control group; N=19). For the clinic resting BP control, we observed that 90% versus 10% of the participants controlled BP in the SMASK and control groups, respectively. Overall attrition was 10% in the intervention group [69].

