## Results

The SMASK project received funding from NIDDK in June 2016, obtained institutional review board approval in April 2016, and began data collection in July 2016. As of July 2018, we have completed enrollment with a total sample size of 80 participants. Currently, we are analyzing baseline data and upon completion of analysis of the final participant in the 6-month active trial, we will begin analyzing preliminary data to be submitted for peer-review publication.

Approval for important protocol modifications will be sought from the institutional review board. Written informed consent was obtained from all patients before enrollment by a trained research coordinator. There are no anticipated risks associated with participation in the study. Patients are free to withdraw at any time. Data will be kept confidential and anonymized for analyses.

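### Adherence outcome: the SMASK tray both reminds and measures, so the available-data model rests the month-3 result on patients still on the tray and could overstate the SMASK rate

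*Protocol article*

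**What the plan says.** The adherence endpoint is the proportion of patients who reach and keep monthly tray scores above 0.90 (Protocol article, Outcome Measures). In the SMASK arm the same tray gives the escalating reminders (Mobile Health Intervention). Standard care (SC) uses the tray with reminders off for 6 months (Attention Control Standard Care Group).

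On scoring, "a missed dose will be assigned a score of 0" (Calculation of Adherence Score). On leaving, "Patients are free to withdraw at any time" (Results).

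Statistical Analyses, Primary Outcome Measures, puts all randomized subjects in the ITT set and says that "all available data points will be included in the model". The model is a mixed-effects model with the physician as the only named random effect, and the main comparison is at 3 months. Multiple imputation is named only for two exploratory outcomes, eGFR and 24-hour BP.

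The sample-size section makes its claim on the full randomized number: "In intent-to-treat (ITT) analysis, with 40 patients per group". It also reports the pilot: "Overall attrition was 10% in the intervention group".

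**The concern.** In the SMASK arm, giving up the tray ends both the reminders and the measurement, so the reason a score is missing is tied to the outcome. These patients were enrolled because they scored below 0.85 with reminders off. It is hard to assume that, once the reminders end, they would do as well as patients who still receive them. An available-data model makes roughly that assumption. With only a physician effect named, a leaver's own earlier scores would not inform that leaver's month-3 value.

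The scoring rule adds an inconsistency. A tray left connected but unopened counts as failure, while a tray returned or switched off leaves nothing to score. Two patients who have both given up the tray are then counted differently.

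At stake are the size of the month-3 adherence difference and what it passes on, because the article intends to use these estimates to plan a multisite trial.

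**Working it through.** **The plan's own figure.** The claim is that "a two-sided Chi-square test (α=0.05) will have >90% power to detect a difference of 35% in proportions". Base rates are not stated, so SC rates from 0% to 65% were tried with 40 per group. Exact power of the Pearson chi-square test is 0.904 or more throughout. The normal approximation gives 0.894 to 0.993, and the minimum with continuity correction is 0.858. The claim reproduces.

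**Inputs.** From Proposed Sample Size: 40 per group, a 35-point difference, 10% SMASK attrition and 89% SMASK success (the last two from the pilot). Assumed: the SC rate *c*, the outcomes of leavers, and no loss in SC.

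**Formulas.** Let *s* be SMASK success among those still on the tray and *d* the SMASK loss. The available-data rate is *s*. Over all randomized patients:

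- leavers revert to the SC rate: rate = (1 − *d*)*s* + *dc*, so the overstatement is *d*(*s* − *c*);
- all leavers fail: rate = (1 − *d*)*s*, so the overstatement is *ds*.

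**Results at *d* = 10%.** Reverting leavers: 0.10 × 35 = 3.5 points. All leavers failing: 0.10 × 45 = 4.5 points at 45% success, up to 0.10 × 89 = 8.9 points at 89%.

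The all-randomized difference behind a 35-point on-tray difference, with exact power at 40 per group:

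| SC rate | SMASK on tray | Leavers revert: difference (power) | Leavers fail: difference (power) |
|---|---|---|---|
| 10% | 45% | 31.5 (0.923) | 30.5 (0.909) |
| 20% | 55% | 31.5 (0.851) | 29.5 (0.804) |
| 32.5% | 67.5% | 31.5 (0.833) | 28.3 (0.745) |

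**Loss in SC.** If SC loses a fraction *d₀* and all leavers in both arms fail, the net overstatement is *ds* − *d₀c*. With 10% lost in each arm it is 0.10 × 35 = 3.5 points. It changes sign when *d₀* exceeds *ds*/*c*: at 55% against 20% that is 0.055/0.20 = 27.5% SC loss, and at 67.5% against 32.5% it is 0.0675/0.325 = 20.8%.

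**Does a repeated-measures model remove it?** In a small simulation on assumed values, 10% of SMASK patients had no month-3 score and reverted to their off-system level. The true all-randomized difference in mean score was 0.269. The available-data fit gave 0.300 without a patient effect and 0.300 with one.

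**False positives.** With no all-randomized effect, all SMASK leavers failing and SC fully observed, the rejection rate at *d* = 10% is 0.046 to 0.078 for success rates of 10% to 50%.

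**The pilot line.** It is given as "89% (versus 0% in control group; N=19", while the Introduction puts 20 patients in the pilot. 8/9 = 88.9% fits one SMASK leaver dropped from ten; over all randomized it would be 8/10 = 80%. Arm counts are not printed, so this is an inference.

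**The case against.** An all-randomized set analysed by a mixed model on all observed data is standard practice and is not a contradiction. Detailed missing-data rules often sit in an SAP, which is not shown. That is fair as far as omissions go. Here, though, the article does state the rule for the primary outcomes, and the rule suits an outcome whose meter is part of the treatment poorly.

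A reader might infer that any patient who stops engaging with SMASK stops being measured. The article does not support that. Unopened compartments on a connected tray score 0, and nothing says that ignoring messages or home BP reminders ends recording. The gap covers only withdrawn patients and trays returned or switched off.

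A reader might also infer that the SMASK estimate will be inflated, by about 9 points. That is not shown either. SC patients use the same tray, receive texts every 3 days, and are handled by the same rule. The article does not say which arm will lose more. The 9-point figure needs 89% success, failure of every SMASK leaver and no SC loss. The 10% attrition comes from a very small pilot.

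Finally, the wording about sustaining adherence might be read as conflicting with the available-data rule. Nothing in the article carries an early success forward, so no conflict is shown.

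Clinic SBP is measured with a separate device at clinic visits, so this mechanism does not reach it. Follow-up of all subjects for clinic BP and medication possession ratio to month 12 is already planned.

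**Conclusion.** The point holds for the tray-derived adherence outcome only. The stated rule in effect estimates month-3 success from patients still on the tray, under a missing-at-random assumption that is doubtful in the SMASK arm, where losing the tray also means losing the reminders.

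It could overstate the SMASK rate. With 10% SMASK loss and none in SC, the plausible range is about 3.5 points (reverting leavers, 35-point on-tray difference) to 4.5 to 8.9 points (all leavers failing). Bias of that size could not by itself create a 35-point difference. If the 35 points describe patients on the tray, exact power over all randomized patients is about 0.75 to 0.92 in the cases tabulated. If they already describe all randomized patients, the stated power stands.

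The conclusion rests on assumed leaver outcomes, on pilot attrition, and on reading an unplugged tray as giving no score. Large enough SC loss, with SC leavers also failing, would reverse the direction.

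**What to change.** In Statistical Analyses, Primary Outcome Measures, define the month-3 adherence result for every randomized patient in both arms. A patient with no tray score because the tray was stopped or returned, or because the patient withdrew, counts as not reaching and keeping a score above 0.90. The denominator in each arm is all patients randomized to it. State how a disconnected tray is told apart from a connected but unopened one; the fidelity checklist in Table 1 already lists tray connection and reloads.

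Report the available-data mixed model as a sensitivity analysis, with a tipping-point check on the outcomes of patients without scores and a cross-check against the medication possession ratio already scheduled at month 3.

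The cost is wording and analysis time, with no new assessment. Success proportions would be slightly less favourable, and the rule is conservative for patients lost for unrelated reasons. The definition should be settled before month-3 results are compared between arms.

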**Potential moderators/mediators**								
	Demographics	Age, education level, income, type of health care insurance	✓		✓	✓	✓	✓
	Anthropometrics	Height, weight, girth	✓	✓	✓	✓	✓	✓
	Health literacy	Health Literacy Scale [59-62], correlated with short test of functional health literacy in adults. Three questions compared to those in the Short Test of Functional Health Literacy in Adults to detect inadequate health literacy: areas under the receiver operating characteristic curve were 0.76, 0.80, and 0.87. When correlated with Short Form-36 (*r*=0.86-0.87), it differentiates between healthy status and various types of illnesses (eg, migraine vs healthy using components: physical and mental quality of life; all *P*<.001)	✓					

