### Allocation and Concealment

Subject randomization will be stratified by race and gender and will be conducted by a statistician using a computer-generated random sequence of numbers. Participants who consent to the study and are eligible for randomization at the conclusion of the 1-month medication intake screening period are allocated to either the intervention (SMASK) or SC arm using the computer-generated randomization sequence. Each random sequence is kept concealed in an envelope that is opened by the research coordinator at the time of randomization.

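### Randomisation is stratified by race and gender, but the stated primary model contains neither factor; if either is prognostic, the 3-month comparison loses a little power

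*Protocol article*

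**What the plan says.** Allocation and Concealment states: "Subject randomization will be stratified by race and gender".

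Statistical Analyses, Primary Outcome Measures, describes the primary analysis as a "simple mixed-effects model containing the fixed time and intervention group, time, and time-by-intervention as primary independent variables", with "MD as a random effect to account for clustering". The contrast of interest is given there too: "The main analysis will compare the two intervention groups (SMASK vs SC) at the primary time point outcome at 3 months". A separate secondary/exploratory step then examines covariates, "including self-determination theory tenants, demographic and clinical characteristics, and comorbidities".

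Table 1 lists the demographic variables among potential moderators and mediators as "Age, education level, income, type of health care insurance". Race and gender are not in that row.

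The power statement in Proposed Sample Size rests on an unadjusted test: "with 40 patients per group", "a two-sided Chi-square test (α=0.05) will have >90% power to detect a difference of 35% in proportions". Both primary outcomes are proportions.

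**The concern.** Stratifying the allocation balances the arms on race and gender. That balance reduces the true sampling variance of the treatment difference when the factors are prognostic. An analysis that leaves them out does not see the reduction: on the risk-difference scale it keeps the between-stratum variance in its error term. The test then rejects less often than its nominal level under the null, and it has less power than a test that uses the design.

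The article does more than stay silent about covariates. It names the terms of the primary model and places demographic adjustment in a later, exploratory step. So the mismatch between design and analysis lies in what is stated. At stake is some precision in a trial of 80 patients. False positives are not at issue.

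**Working it through.** **Inputs from the article.** 40 per group, two-sided alpha 0.05, 35-point difference, power above 90%, binary outcomes, contrast at 3 months. The control proportion is not stated. Nor is any association of race or gender with outcome, so both are varied.

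**Step 1: the plan's own figure.** Power = Φ[(d − 1.96·SE0)/SE1], with SE0 = √(2p̄(1−p̄)/n) and SE1 = √([p1(1−p1)+p2(1−p2)]/n).

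The least favourable case is 32.5% vs 67.5%. SE0 = √(2×0.25/40) = 0.1118 and SE1 = √(2×0.2194/40) = 0.1047. Then (0.35 − 0.2191)/0.1047 = 1.25, which gives 89.4%. Other cases: 0% vs 35%, 99.3%; 10% vs 45%, 95.4%; 20% vs 55%, 91.4%; 25% vs 60%, 90.2%. The stated figure reproduces for control proportions up to about 25% or from about 40%, and is less than 1 point short in between.

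**Step 2: effect of leaving the strata out, by formula.** Let the strata explain a share R² of the within-arm outcome variance. With 1:1 blocked allocation within strata (assumed), the unadjusted standard error on the risk-difference scale is too large by the factor 1/√(1−R²). Take θ = 1.25 + 1.96 = 3.21 from the least favourable case. Then:

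- actual alpha, unadjusted = 2Φ(−1.96/√(1−R²))
- power, unadjusted = Φ[(θ − 1.96)/√(1−R²)]
- power, adjusted = Φ[θ/√(1−R²) − 1.96]

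| R² | SE too large by | Actual alpha, unadjusted | Power, unadjusted | Power, adjusted |
|---|---|---|---|---|
| 0 | 0% | 5.0% | 89.4% | 89.4% |
| 0.02 | 1.0% | 4.8% | 89.7% | 90.0% |
| 0.05 | 2.6% | 4.4% | 90.0% | 90.9% |
| 0.10 | 5.4% | 3.9% | 90.6% | 92.3% |
| 0.20 | 11.8% | 2.8% | 91.9% | 94.8% |

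For R² = 0.20, √0.80 = 0.894. Unadjusted power is Φ(1.25/0.894) = Φ(1.40) = 91.9%; adjusted power is Φ(3.21/0.894 − 1.96) = Φ(1.63) = 94.8%.

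**Step 3: simulation on the risk-difference scale.** 3,000 trials per setting, blocks of 4 within four race-by-gender strata, stratum shares 60% and 50% (all assumed), 35-point effect, fits with and without race and gender.

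| Stratum effect per factor | Mean SE, unadjusted / adjusted | Power, unadjusted / adjusted | Null rejection, unadjusted |
|---|---|---|---|
| 0 points | 0.105 / 0.105 | 89.1% / 88.8% | 5.0% |
| 10 points | 0.105 / 0.103 | 90.3% / 89.9% | 4.4% |
| 20 points | 0.105 / 0.100 | 91.1% / 92.0% | 3.9% |
| 30 points | 0.105 / 0.094 | 91.9% / 94.9% | 2.8% |

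The two tables agree. A 30-point effect for each factor gives a between-stratum variance of 0.09×(0.6×0.4) + 0.09×(0.5×0.5) = 0.0441. Divided by 0.2194, this is R² = 0.20.

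**Step 4: cost when nothing is prognostic.** Model adjustment costs 89.1 − 88.8 = 0.3 points. A Cochran-Mantel-Haenszel test in place of the chi-square costs 90.3 − 89.6 = 0.7 points in 20,000 runs at 35 points. One smaller run put the cost of the stratified test as high as about 1.5 points.

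**The case against.** Several objections limit the point, and most of what they say stands.

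- *The loss is conditional.* A reader might infer that the primary standard error is too large and that power is being thrown away. The article shows no link between race or gender and either outcome. With no link, nothing is lost.
- *The standard-error statement belongs to the linear scale.* The outcomes are binary. In a logistic model, adjustment raises the standard error of the log odds ratio: 0.48 unadjusted against 0.49, 0.50, 0.53 and 0.59 adjusted, for stratum effects of 0, 10, 20 and 30 points. Power can still rise because the conditional effect is larger (91.8% to 94.8% at 30 points), but the standard error does not shrink.
- *The conservatism needs blocking.* The article mentions only a computer-generated sequence. With unrestricted sequences within strata and differences of 30 points by race and 20 by gender, the unadjusted chi-square test rejects about 5.6% of the time under the null. The conservatism disappears, though a power gain from adjustment remains.
- *Larger losses can be shown only off-plan.* For a 25-point effect, one simulation gives 65.7% vs 69.4% (strata of 30 and 20 points) and 61.6% vs 68.1% (40 and 20 points). The plan is for 35 points, where the 30/20 setting gives 92.0% vs 93.6%.
- *The article is condensed.* It does not spell out a patient-level random effect or covariance structure, so the list of terms may be incomplete. This weakens the point but does not remove it, because demographic covariates are explicitly placed in a later step. The Table 1 row is weak evidence, since it lists moderators and mediators.
- *The calculations are simpler than the planned model.* They treat the 3-month contrast as one comparison, without repeated measures or the physician effect, because no variance components are given.

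**Conclusion.** The mismatch is real and its consequence is modest. The stated primary model omits both stratification factors. If they explain 0 to 20% of outcome variance and allocation is blocked within strata, actual alpha lies between about 5.0% and 2.8%, and adjustment gains about 0 to 3 points of power at the planned 35-point difference. If neither is prognostic, adjusting costs about 1 point or less at that difference.

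A reader might go on to infer that the claim of more than 90% power fails, or that a positive result would be suspect. Neither follows. The power claim comes from an unadjusted chi-square test, and in the cases examined prognostic strata with blocked allocation raised the unadjusted power (89.4% to 91.9% in the formula). Where the error rate is off under blocking, it is off in the conservative direction. This is a precision improvement that aligns the analysis with the design.

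**What to change.** Add race and gender as fixed effects to the primary mixed-effects model in Statistical Analyses, Primary Outcome Measures.

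As a supportive analysis of the 3-month proportions, report the Mantel-Haenszel risk difference with a Cochran-Mantel-Haenszel test stratified by race and gender. It stays estimable if the standard care arm has no successes, as happened for adherence in the pilot (0%). It should remain supportive, because it drops the repeated-measures and physician structure that the plan chose.

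The models under Secondary Outcome Measures already adjust for demographic characteristics. They need only a check that race and gender are among them.

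The cost is one sentence. Both factors are known for every randomised patient, because the allocation used them. Two degrees of freedom are spent if race is coded in two levels, and more otherwise; the article does not give the levels. The Results section says that only baseline data were being analysed at the time of writing, so on that account the change could still be pre-specified.

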### Study Participants

The participants are adult kidney transplant recipients with uncontrolled hypertension who have met the inclusion/exclusion criteria. Potentially eligible study patients were identified through weekly data extractions from the appointment database.

The inclusion criteria for participants were age >18 years (male or female), first- or second-time recipient of a functioning solitary kidney transplantation performed 6 weeks to 60 months earlier, legally competent, assent provided by the transplant physician so that the patient is able to participate, patient prescribed ≥3 medications for immunosuppression and hypertension, electronic pill tray–based medication adherence score <0.85 across a 1-month screening period, uncontrolled systolic hypertension (SBP ≥130 mm Hg) at the screening visit and baseline evaluation (following 1-month medication monitoring period), and 24-hour ambulatory SBP ≥130 mm Hg following the medication monitoring period.

The exclusion criteria were severe cognitive impairment/dementia; inability to self-administer medications, self-measure BP, or use a mobile phone; poor cellular coverage at home; inability to speak, hear, or understand English; history of psychiatric illness or substance abuse; planned pregnancy; and vulnerable populations such as pregnant or nursing women, prisoners, and institutionalized individuals.

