### Identification of Medication Nonadherent Patients with Uncontrolled Hypertension

Patients who meet the initial eligibility criteria, including a resting BP evaluation (SBP ≥130 mm Hg), and provide informed consent will be enrolled in a 30-day screening period using the SimpleMed+ with its reminder functions disabled. Subjects will be given a demonstration of how to properly use the medication tray and will be required to demonstrate successful use of the tray before completion of the visit. They will receive written and oral instructions explaining that to be considered fully adherent, they must take their medications within 90 minutes of the prescribed dosing time. After confirming successful connection with the server, the tray will be programmed by the study manager to accurately reflect the subjects’ medication dosing schedule. At the conclusion of the 1-month screening period, our modification [25] of the adherence equation by Russell et al will be used to calculate a medication adherence score for each subject. Only subjects with a cumulative adherence score <0.85 across the 1-month screening period will be eligible for randomization to either the mHealth intervention group or the attention control SC group.

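### The primary 3-month comparison leaves out pre-randomisation clinic SBP and the screening-month adherence score, which every eligible patient has; it stays valid but gives up a modest amount of precision

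*Protocol article*

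**What the plan says.** Under Statistical Analyses, Primary Outcome Measures, the protocol article describes the primary analysis as a simple mixed-effects model "containing the fixed time and intervention group, time, and time-by-intervention as primary independent variables (fixed effects"), with "MD as a random effect to account for clustering". The contrast is stated as "The main analysis will compare the two intervention groups (SMASK vs SC) at the primary time point outcome at 3 months". Other variables come in later: "In secondary/exploratory analysis for aim 1 outcomes, the potential influence of" pre-specified covariates is to be explored, "including self-determination theory tenants, demographic and clinical characteristics, and comorbidities". Neither baseline SBP nor the screening adherence score is named there.

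Both measures exist before randomisation because entry depends on them. Study Participants requires "uncontrolled systolic hypertension (SBP ≥130 mm Hg) at the screening visit and baseline evaluation" and a "medication adherence score <0.85 across a 1-month screening period". The section on identifying nonadherent patients repeats the second condition: "Only subjects with a cumulative adherence score <0.85 across the 1-month screening period will be eligible for randomization". Allocation and Concealment stratifies by race and gender only. Under Outcome Measures, both primary endpoints are proportions: sustained resting SBP below 130 mm Hg, and sustained monthly adherence above 0.90.

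**The concern.** How far a patient starts from the target should bear on reaching it. A patient at 132 mm Hg needs a fall of 3 mm Hg to read 129; a patient at 165 needs 36. A comparison that ignores the starting value treats that predictable variation as noise. With 40 patients per arm and no stratification on SBP or adherence, the arms can also differ at baseline by chance, and the unadjusted estimate carries the difference. At stake is power in a small trial, and how convincing the result will look if the arms turn out visibly unequal. This is not simply a detail left to an unseen analysis plan: the article itself states the primary model and assigns covariates to exploratory work. It does name adjustment variables for the secondary outcomes.

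**Working it through.** **1. The plan's own power.** Proposed Sample Size claims more than 90% power with 40 per group, two-sided alpha 0.05 and a 35-point difference. It gives no planning control rate, so I tried several. Power = Φ{[Δ√n − 1.96√(2p̄(1−p̄))] / √(p₁q₁ + p₂q₂)}. For 32.5% v 67.5%: Δ√n = 0.35 × 6.325 = 2.214; 1.96 × √0.5 = 1.386; √(2 × 0.325 × 0.675) = 0.662; (2.214 − 1.386)/0.662 = 1.25, so power is 89.4%. This is the worst case. At 20% v 55% it is 91.4%, and at 10% v 45% it is 95.4%. The claim reproduces to within about a point. With 36 per arm (10% lost, as in the pilot's intervention group) the worst case is 86.0%.

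**2. Does a preintervention time point adjust the proportions?** At entry SBP is at least 130 and adherence is below 0.85, which is below 0.90. Each binary outcome is therefore 0 for every patient in both arms. A constant has no variance and no covariance with the month-3 outcome, so it adjusts for nothing. On the continuous scale, free group-by-time means with complete data give essentially the raw month-3 difference in means.

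**3. Chance imbalance.** The standardised baseline difference between arms has SD √(2/40) = 0.224. The chance that it exceeds 0.25 SD is 26%, and that it exceeds 0.4 SD is 7%. A 0.25 SD imbalance shifts the unadjusted risk difference by 1.4 to 1.8 points if baseline and outcome correlate at 0.2, and by 3.9 to 5.4 points at 0.6.

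**4. Precision at the planned effect.** Simulation: 20,000 trials, 40 per arm, true difference 35 points, one baseline SBP from a normal (mean 140, SD 15) truncated at 130, latent month-3 value with correlation ρ, linear adjustment. All these values except the arm size, the effect and the threshold are assumed.

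| ρ | Variance cut, risk difference (10% v 45%; 32.5% v 67.5%) | Power at 32.5% v 67.5%, unadjusted → adjusted |
|---|---|---|
| 0.2 | 0.8%; 0.8% | 90.4% → 89.8% |
| 0.3 | 2.5%; 3.5% | 90.6% → 90.8% |
| 0.4 | 5.5%; 7.9% | 89.9% → 91.6% |
| 0.5 | 8.7%; 12.6% | 90.1% → 93.1% |
| 0.6 | 12.1%; 20.1% | 90.6% → 95.2% |

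**5. Precision with two qualifying visits.** Assumed: untruncated mean 145, SD 16, between-visit correlation r from 0.4 to 0.7, both pre-randomisation readings at least 130, covariate the mean of the two.
- SBP below 130 with a 12 mm Hg effect: variance cut about 3% to 12%, power gain about 2 to 5 points.
- Continuous month-3 SBP: variance cut about 12% to 44%.
- Adding the ambulatory SBP criterion (assumed mean 130 to 140, SD 14, correlation about 0.9 with the true level): in the run that examined this, the binary cut fell from 6–13% to 2–10%, the power gain fell to about 1 to 4 points, and the continuous cut at r = 0.4 fell from 14% to 9–11%.

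**6. Adherence.** The document gives no correlation between the screening score and month-3 adherence, and all scores are truncated below 0.85. No figure can be derived.

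**The case against.** The case for leaving the plan alone is substantial. The unadjusted contrast is unbiased over randomisation, and its standard error already allows for chance imbalance; imbalance and lost precision are one cost, not two. All of this stands.

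A reader might take the large continuous gains as the size of the problem. They belong to a supporting analysis, because the primary endpoints are proportions, where the gain is small. A reader might also add a large gain over change from baseline. In the two-visit simulation a cut of 24% to 27% appears, but only when adjustment for the mean of two visits is set against change from one; with the same baseline in both it is only about 1% to 9%. Similarly, the between-arm baseline SBP difference has SD about 2.8 mm Hg for one visit but 2.2 to 2.5 for the two-visit mean.

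It is also tempting to infer that baseline values are shut out of every analysis. The exploratory list is open-ended and mentions clinical characteristics, which could include baseline SBP. What stands is that this would not touch the primary result.

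Finally, adjustment is not wholly without cost. The pilot control arm had 0% adherent and 10% with controlled BP. With few successes, a baseline-adjusted logistic test rejected in 5.6% to 8.1% of null simulations, against 5.9% to 6.5% for chi-square. That is a reason to choose the method with care, not to ignore the baseline.

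**Conclusion.** The point holds as a modest loss of precision, not as an error. The stated primary model omits two baseline measures the trial already has, and the preintervention time point does not stand in for them on the binary endpoints. For SBP below 130 mm Hg, the 3% to 12% variance reduction depends on the assumed SBP distribution and correlations, and a weaker baseline-outcome correlation would leave almost no gain. The benefit for adherence is plausible but unquantified. The document does not support calling the planned comparison biased or invalid, or describing the trial as seriously underpowered for want of adjustment.

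**What to change.** In Statistical Analyses, Primary Outcome Measures, state that the primary SBP analysis adjusts for continuous pre-randomisation clinic SBP (mean of the screening and baseline readings), and the primary adherence analysis for the continuous 30-day screening score. Report a standardised, baseline-adjusted risk difference at 3 months, and name a method that remains stable when control-arm successes are few. For the longitudinal continuous models, either adjust for baseline or fit a common preintervention mean across arms.

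The cost is wording, slightly more analysis work and care with sparse cells; no new data, visits or patients are needed. The covariates should be fixed before outcomes are examined by arm. The Results section indicates that, when the article was written, baseline data were being analysed and preliminary analysis was still to come, so there was time to do this. Covariates added after results are seen would invite a charge of selective adjustment.
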